#### Secondary analyses

A similar repeated measures ANOVA approach will be used to examine intervention effects on obesogenic behaviors. The within-subjects and between-subjects factors will be identical to those in the primary model above and the dependent variables will be diet and physical activity. We will also examine dose-response effects of the interventions using regression models predicting 12 month BMI percentile from the number of doses of intervention received controlling for baseline BMI percentile. Linear mixed modeling will be used to determine if maternal (depression, perceived stress, health care climate) and family (food insecurity, acculturation) characteristics have main effects on change in BMI percentiles and, of greater interest, if they moderate treatment group effects. In this analysis, BMI percentiles at baseline and 12 months will be used as a repeated variable, intervention group will be used as a fixed subject variable, and maternal and family characteristics will be covariates (first individually and then jointly) to examine how they relate to changes in weight across the sample. Then, interactions between intervention group and maternal and family characteristics will be entered into the model to determine if any maternal/family characteristics moderate the effect of intervention group on changes in BMI percentiles. Multiple regression analyses will be used to determine if clinician’s attitudes towards obesity, BMC self-efficacy, hope and conscientiousness and outcome expectancy predict the number of doses of BMC that they deliver. Finally, as Steps to Growing Up Healthy represents an example of a “practical trial” we plan to evaluate the RE-AIM criteria (Reach; Effectiveness; Adoption; Implementation; Maintenance) [60] by looking at indicators such as the percentage of mothers approached about the study who enroll, the percentage of mother-child dyads who receive more than one dose of BMC, and the number of signed action plans.

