### Outcome measures

The following measures are administered at baseline and 12 months unless otherwise noted.

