##### Diet and physical activity

We are using the parent-report 24-item Children’s Dietary Questionnaire to assess dietary quality [43]. This measure is appropriate for preschool age children and all subscales have demonstrated satisfactory test-retest reliability and an ability to detect change in the expected direction following a weight management intervention. To assess physical and sedentary activity, we are using a brief 12-item questionnaire by Spurrier et al. [44] based on the Outdoor Playtime Checklist. The questionnaire assesses outdoor playtime and has been validated against objective accelerometer data. It also assesses sedentary activity focusing on small screen entertainment (i.e., time spent watching TV and playing video games). This measure has been used in prior studies of preschool aged children and is sensitive to change over time. In addition, the Steps to Growing Up Healthy Survey, a 16-item questionnaire developed specifically for this study is administered at every clinic visit to assess the 4 target areas as well as the child’s general health habits (e.g., water consumption, sleep).

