### Statistical analysis

#### Primary analysis

We will use an-intent-to-treat approach to data analysis. All randomized children will be included in the analyses regardless of whether they receive any actual intervention. We will impute BMI percentile change among attritors using their historical heights and weights obtained through chart review; however, we also will conduct treatment completer analyses using only complete cases. Baseline variables (e.g., demographics) will be compared between intervention groups using chi-square statistics and *t*-tests to determine if any group differences exist despite randomization. Baseline variables that differ between groups will be included as covariates in subsequent analyses.

Repeated measures analysis of variance models will be conducted to address the research questions. In the primary analysis, the dependent variable will be BMI percentile. In this model, the within-subject factor will be time, which will include 2 levels (baseline and 12 months). Between-subjects factors will include treatment group (BMC, BMC + Phone, and BMC + Home). Demographic variables that are found to differ across groups will be included as covariates.

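### As written, the diet and activity analysis is a complete-pair change-score analysis: the all-randomised rule has a stated means only for BMI percentile, and baseline-dependent dropout that differs by arm would bias the behaviour comparison modestly.

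*Protocol article*

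**What the plan says.** Under Primary analysis, the Protocol article adopts intention to treat and adds: "All randomized children will be included in the analyses regardless of whether they receive any actual intervention". The means given for families who leave is: "We will impute BMI percentile change among attritors using their historical heights and weights obtained through chart review". A separate analysis is then announced: "we also will conduct treatment completer analyses using only complete cases". The article therefore treats complete-case analysis as something other than its intention-to-treat analysis. The primary model is a repeated measures ANOVA with time at two levels, baseline and 12 months.

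Under Secondary analyses, behaviour is handled the same way: "A similar repeated measures ANOVA approach will be used to examine intervention effects on obesogenic behaviors". The factors are "identical to those in the primary model above and the dependent variables will be diet and physical activity". The Outcome measures section gives the timing: "The following measures are administered at baseline and 12 months unless otherwise noted". Diet is a 24-item parent-report questionnaire and activity a 12-item one. Linear mixed modelling appears in Secondary analyses, but only for predictors and moderators of BMI percentile change.

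**The concern.** Charted heights and weights can supply a BMI percentile but not a questionnaire score. The article names the model, the time levels and the outcomes for behaviour, and that model on its own uses only families with both values. The result is the kind of analysis that the article sets apart from intention to treat.

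The four behaviours are the direct targets of the counselling, so these results will be read as explaining any BMI effect. BMI would be reported on all children and behaviour on completers. Loss could plausibly differ by arm: the two community health worker arms have monthly contact and up to $60 in contact payments, and BMC alone has neither. If families with poorer habits also leave more often, a comparison of raw change is distorted.

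**Working it through.** **Families used.** Inputs from Sample size and power: 50 per arm, 150 in total, with dropout of 15% (planned) and 25% (worst case considered).

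- 15%: 150 × 0.85 = 127.5 used (42.5 per arm), 22.5 left out.
- 25%: 150 × 0.75 = 112.5 used (37.5 per arm), 37.5 left out.

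The article states no sample size or power for diet or activity, so there is no figure of its own to reproduce here.

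**What the ANOVA estimates.** With two time levels, the group-by-time test is the same as a one-way ANOVA of change (12 months minus baseline) in families with both values.

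**Bias.** Assumptions, none of them from the article: scores standardised, higher meaning poorer habits; no true effect; baseline to 12-month correlation ρ of 0.4 or 0.6; log-odds of dropout rising by 0.7 or 1.1 per SD of baseline; loss of 25% in BMC against 5% or 10% in BMC + Home. Dropout depends on the baseline score only, so among completers the expected 12-month score is ρ × baseline, and

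false difference in change = (ρ − 1) × (completers' baseline mean in Home − completers' baseline mean in BMC).

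Simulation with 2 million families per arm:

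| ρ | Log-odds per SD | Loss BMC / Home | Completers' baseline mean, BMC | Same, Home | False difference in change (SD) |
|---|---|---|---|---|---|
| 0.4 | 1.1 | 25% / 5% | −0.229 | −0.051 | −0.108 |
| 0.4 | 1.1 | 25% / 10% | −0.227 | −0.099 | −0.077 |
| 0.4 | 0.7 | 25% / 5% | −0.161 | −0.035 | −0.075 |
| 0.4 | 0.7 | 25% / 10% | −0.161 | −0.066 | −0.055 |
| 0.6 | 1.1 | 25% / 5% | −0.228 | −0.051 | −0.071 |
| 0.6 | 1.1 | 25% / 10% | −0.228 | −0.098 | −0.052 |
| 0.6 | 0.7 | 25% / 5% | −0.160 | −0.033 | −0.051 |
| 0.6 | 0.7 | 25% / 10% | −0.160 | −0.067 | −0.038 |

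Formula check, first row: (0.4 − 1) × (−0.051 + 0.229) = −0.107. In these scenarios the error favours Home. With equal loss (15% or 25% in both arms) it was within about 0.002 of zero.

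**Cause.** On the same data, ANCOVA of the 12-month score on baseline, using the same completers, gave a difference within about 0.002 of zero. So did a likelihood estimate that kept the baseline-only families. Conditioning on baseline is what removes the bias.

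**Precision.** In SD units, the standard error of an arm difference is √[2 × 2(1 − ρ)/n] for change and √[2(1 − ρ²)/n] for ANCOVA. With ρ = 0.5 and n = 37.5 per arm these are √(2/37.5) = 0.23 and √(1.5/37.5) = 0.20.

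**Bias against noise.** For change with unequal loss, SE = √[2(1 − ρ)(1/n₁ + 1/n₂)].

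- Largest case (ρ 0.4, n 37.5 and 47.5): SE 0.239, ratio 0.107/0.239 = 0.45.
- Smallest case (ρ 0.6, n 37.5 and 45): SE 0.198, ratio 0.038/0.198 = 0.19.

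A two-sided 5% test then has a type I error of about 7.3% and 5.4% respectively.

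**The case against.** A reader might infer that the article contradicts itself and that intention to treat cannot hold for behaviour. The text does not carry that. The all-randomised sentence sits under Primary analysis, beside a BMI-only rule, and speaks of children who receive no intervention. Secondary analyses never labels the behaviour results intention to treat. Naming an ANOVA does not forbid imputation, since the article combines the same model with imputation for BMI. Missing-data detail for secondary questionnaires may also stand in a fuller document. All of this stands and limits the point. What remains is that the rule is worded generally, its only stated means cannot reach these outcomes, and the chosen model is a weak one for them.

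A reader might also infer that the harm comes from dropping baseline-only families. It does not: the complete-case ANCOVA discards the same families and is unbiased in the same scenarios. Those families have no 12-month score under any model.

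Finally, a reader might see unused data in the Steps Survey, "a 16-item questionnaire developed specifically for this study is administered at every clinic visit to assess the 4 target areas". It is a different instrument, collected at irregular visits as the first step of the counselling. It is listed under the diet and activity measures, and nothing clearly excludes it as an outcome. Using it, or collecting the 12-month questionnaires by phone, is a preference and no part of this point.

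**Conclusion.** The point holds in limited form. Without imputation, the behaviour analysis as described is a complete-pair change-score analysis of about 112 to 127 of 150 families, and the article's stated means of including all randomised children does not reach it. The bias is conditional and modest: about 0.04 to 0.11 SD, or roughly 0.2 to 0.45 of a standard error. It arises only if dropout depends on baseline behaviour and also differs by arm. The arm-specific rates, the dependence on baseline and the correlation are all assumptions. With equal loss, what remains is lost precision. The primary BMI outcome is not affected.

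**What to change.** Analyse diet and activity with a likelihood-based linear mixed model with time and arm-by-time terms and a common baseline mean across arms, keeping all randomised families, including those with a baseline score only. Equivalently, use ANCOVA of the 12-month score on the baseline score, with imputation of missing scores. Both kinds of model are already named in the article: mixed modelling for moderators, and ANCOVA in the sample size section. Label the repeated measures ANOVA on complete pairs as a completer analysis. State whether the all-randomised rule covers the secondary outcomes.

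The cost is a few sentences of text and slightly more analysis work, with no new data collection. The analysis then relies on missingness at random given the observed data, which should be stated.

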**Figure 2 F2:**
[figure not shown]
Steps to growing up healthy behavior target clinical tool.

To encourage medical teamlets to use BMC with their patients, clinicians and nurses receive $10 each time they provide a BMC dose. The clinician/nurse must document the child’s BMI percentile, discuss an obesogenic behavior from the Steps to Growing Up Healthy Survey using BMC, and create a Steps to Growing Up Healthy Action Plan in concert with the family to receive the incentive. Over the course of the 12-month intervention period, we anticipate that families will receive 3-5 doses of BMC in the clinic (1-2 well child visits, 1-2 sick visits, and 1-2 WIC check-ins) and 3-5 additional telephone follow-up calls.

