#### Treatment components specific to the added value conditions

##### BMC + Phone

Mother-child dyads randomized to BMC + Phone receive BMC doses at clinic visits as described above plus every month a CHW calls the mother to assess how well the family is doing with their selected behavior change, discuss any barriers the family is experiencing in implementing the behavior change, review the monthly self-monitoring calendar, reinforce positive behaviors, assess the mother’s confidence in achieving her goal, and assist the mother to implement her goal through progressive steps and gradual implementation of new behaviors. Behavioral goals are modified if mothers report having met their goals and/or express interest in selecting a new goal. Each phone call is approximately 10-15 minutes long.

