##### BMC + Home

Mother-child dyads randomized to BMC + Home receive BMC doses at clinic visits as described above plus monthly home visits by a CHW. The focus of these hour long home visits is similar in content to BMC + Phone (i.e., CHWs assess behavior change progress, discuss barriers, review self-monitoring, assist the mother in implementing her goal and/or behavior change by breaking it into small, manageable steps, assess the mother’s confidence in making the behavior change). In addition, the CHW assists the mother with label reading and meal planning, how to structure her home environment to support healthy diet and activity choices, how to determine appropriate portion sizes, and how to enhance physical activity. Activities are visual, interactive, and based on a goal setting and motivational interviewing approach.

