#### Interventionist training

##### Primary care staff

All clinicians and nurses at the PCC (*n* = 32) were invited to participate in the study and receive training in motivational interviewing provided by the study investigators and an external consultant from the Motivational Interviewing Network of Trainers. Clinicians and nurses were asked to attend two 2-hour sessions focusing on key MI strategies such as asking open-ended questions, using reflective listening, positive affirmation, decreasing resistance, and assessing the mother’s interest and confidence in making change. A treatment manual was provided that included a detailed outline of the BMC intervention steps. Mini-booster sessions were conducted periodically at staff meetings and with individual clinicians throughout the intervention period to encourage on-going use of BMC and to assure intervention fidelity. Twenty-four clinicians and nurses provided consent allowing us to collect information about their attitudes towards obesity management and comfort with MI.

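### The dose-response regression names no treatment-arm term and leaves dose undefined, so it can restate the arm comparison as a dose effect if community health worker contacts are counted

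*Protocol article*

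**What the plan says.** The Secondary analyses section states: "We will also examine dose-response effects of the interventions". The method is "regression models predicting 12 month BMI percentile from the number of doses of intervention received controlling for baseline BMI percentile". Two predictors are named, dose and baseline BMI percentile. The moderator model described next in the same paragraph does name arm: "intervention group will be used as a fixed subject variable".

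The contacts a family can receive are described elsewhere in the article:

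- **Clinic BMC, all arms** (BMC section, after Figure 2): "we anticipate that families will receive 3-5 doses of BMC in the clinic". A similar number of short staff follow-up calls goes with them.
- **BMC + Phone:** one CHW call a month. "Each phone call is approximately 10-15 minutes long".
- **BMC + Home:** one CHW home visit a month. "The focus of these hour long home visits is similar in content to BMC + Phone".
- **Retention section:** families in the CHW arms are paid $5 per call or visit, up to $60, so at most 60/5 = 12 CHW contacts. BMC families have none.

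The Adherence and treatment fidelity section records BMC doses, CHW contacts and staff calls as separate counts. The article does not say which of these make up the dose in the regression.

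**The concern.** A dose-response analysis is read as evidence that more contact brings more benefit. That reading needs dose to vary for reasons other than arm. If CHW contacts are included, most of the variation in dose is simply whether the family was randomised to a CHW. A model without arm then attributes the difference between arms to the number of contacts. The trial could report a gradient per contact when families with 6 and with 12 CHW contacts in the same arm do equally well. Advice on how many calls or visits a programme should fund would then rest on the arm comparison restated in other units.

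**Working it through.** The article gives no figure for this regression, so there is nothing to reproduce. The check asks how often the model as written would declare a dose effect when extra contacts within an arm do nothing.

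**Inputs from the article**
- Arm effects 0, -2.5 and -5 percentile points, and alpha 0.05 (taken as two-sided): Sample size and power.
- 50 per arm with 15% dropout: 50 x 0.85 = 42.5, so 42 per arm and N = 126.
- BMC doses 3-5 in every arm; CHW contacts 0 in BMC and at most 12 in each CHW arm.

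**Assumptions**
- Residual SD 5 to 12. As a reference point, the stated 34 per group and 0.85 power imply an SD of about 6.14 if they come from a three-group F test with one covariate.
- BMC doses spread evenly over 3, 4 and 5 (variance 2/3).
- CHW contacts Binomial(12, 0.75) (mean 9, variance 2.25).

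**Case A: dose = BMC doses + CHW contacts**
1. Between-arm variance of dose: (1/3)(2/3)(9^2) = 18.
2. Within-arm variance: 0.667 + (2/3)(2.25) = 2.167. The total is 20.167, so arm accounts for 18/20.167 = 89% of the variation in dose.
3. The mean effect in the CHW arms is (-2.5 - 5)/2 = -3.75. Expected slope without arm: (-3.75/9) x 0.893 = -0.372 points per contact. The true within-arm slope is 0.
4. The arm effects have variance 4.167. Dose absorbs 0.372^2 x 20.167 = 2.79, leaving 1.38 in the residual.
5. SE = sqrt[(SD^2 + 1.38)/(126 x 20.167)] and t = 0.372/SE. The rejection rate is about Phi(t - 1.979).

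| Residual SD | SE | t | Significant, no arm term |
|---|---|---|---|
| 5 | 0.102 | 3.65 | 95% |
| 6.14 | 0.124 | 3.00 | 85% |
| 10 | 0.200 | 1.86 | 45% |
| 12 | 0.239 | 1.55 | 34% |

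Simulation agrees. With attendance varying more between families (2,000 trials per setting), the rates are 94%, 81% and 43% at SD 5, 6.14 and 10, with a mean slope of about -0.34. Across the attendance patterns tried, the figures at the two ends of the SD range move by a few points; about 33-96% is a fair summary. With arm terms the rate is about 5% at every SD and the mean slope is about 0.

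**Case B: dose = BMC doses only, equal attendance.** Dose is then unrelated to arm. Simulated rates are about 5% with or without arm terms.

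**Case C: BMC doses only, but CHW contact adds one clinic dose on average (assumed).**
1. Between-arm variance is 2/9 = 0.222; the total is 0.222 + 0.667 = 0.889.
2. Slope: -3.75 x 0.222/0.889 = -0.94 points per dose.
3. Residual arm variance: 4.167 - 0.94^2 x 0.889 = about 3.39. SE = sqrt[(SD^2 + 3.39)/(126 x 0.889)].
4. At SD 5, SE is 0.503 and t is 1.86, giving about 45%. At SD 12, SE is 1.147 and t is 0.82, giving about 12-13%. Simulation gives 13-46% over this range without arm terms and 5% with them.

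**The case against.** The strongest reply is that dose in this article usually means a clinic BMC encounter. Recruitment and randomization has every dyad receiving its first intervention dose at the enrolment visit, and the Discussion says the doses come from the child's medical team. CHW contacts are called calls, visits or contacts. On that reading Case B applies and nothing is wrong, provided attendance is equal across arms. This stands as a limit on the point. It does not remove it: the same paragraph speaks of doses of intervention here and of doses of BMC for the clinician regression ("predict the number of doses of BMC that they deliver"), and the stated aim concerns the interventions in the plural. Case C shows that even the narrow reading depends on equal attendance.

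A second reply is that an article condenses, and that the plural wording allows separate fits by arm. That is possible. But the model's covariate is stated, and the neighbouring model names intervention group, so the absence of arm here is at least an ambiguity worth closing.

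Three stronger readings are tempting and are not supported:

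- **That all contacts are weighted alike.** Twelve calls take 120-180 minutes and twelve home visits 720 minutes, a 4- to 6-fold gap that a raw sum would ignore. But the article nowhere says that contacts are summed.
- **That a dose effect appears whenever arms differ.** Even with summed contacts, the rate at SD 6.14 is about 4% if Phone and Home differ from BMC by +2.5 and -2.5.
- **That the clinician regression shares the flaw because it names no caseload term.** That is a separate matter. The article gives no caseload data, and bias would need caseload to be correlated with the clinician traits.

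**Conclusion.** The point holds in a conditional form. As written, the model has no arm term and its main predictor is undefined. If CHW contacts count as doses, the planned arm effects alone would produce a significant dose slope in about 33-96% of trials (assumed residual SD 12 down to 5), against about 5% with arm terms. If only BMC doses count, the rate is about 5% under equal attendance, and 13-46% if CHW contact adds one clinic dose on average. These figures rest on assumed SDs, assumed attendance patterns and 42 analysed per arm. The arm term protects under each of these readings. The analysis is secondary and the primary comparison is untouched, but the wording should be settled before the data are analysed.

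**What to change.** Define dose by type of contact and add treatment arm to the model. Enter BMC doses and CHW contacts as separate terms, with the CHW slope estimated within the two CHW arms only. State that the result is associational. The Adherence and treatment fidelity section already records these counts separately, so no new data are needed.

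The cost is a wider interval on the dose slope. Once arm is in the model, only non-randomised variation in attendance within arms remains. That is the information the data hold on dose beyond the arm comparison, and it is open to confounding by why families attend.

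The number of clinic visits attended should not be added as a further covariate. The Discussion expects a BMC dose at every clinic visit, so the two would be nearly collinear.
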